# The effect of audit and feedback and implementation support on guideline adherence and patient outcomes in cardiac rehabilitation: a study protocol for an open-label cluster-randomized effectiveness-implementation hybrid trial

**DOI:** 10.1186/s13012-024-01366-8

**Published:** 2024-05-24

**Keywords:** Cardiac rehabilitation, Cost-effectiveness, Guidelines, Implementation support, Myocardial infarction, Registry, Secondary prevention

## Abstract

**Background:**

Providing secondary prevention through structured and comprehensive cardiac rehabilitation programmes to patients after a myocardial infarction (MI) reduces mortality and morbidity and improves health-related quality of life. Cardiac rehabilitation has the highest recommendation in current guidelines. While treatment target attainment rates at Swedish cardiac rehabilitation centres is among the highest in Europe, there are considerable differences in service delivery and variations in patient-level outcomes between centres. In this trial, we aim to study whether centre-level guideline adherence and patient-level outcomes across Swedish cardiac rehabilitation centres can be improved through a) regular audit and feedback of cardiac rehabilitation structure and processes through a national quality registry and b) supporting cardiac rehabilitation centres in implementing guidelines on secondary prevention. Furthermore, we aim to evaluate the implementation process and costs.

**Methods:**

The study is an open-label cluster-randomized effectiveness-implementation hybrid trial including all 78 cardiac rehabilitation centres (attending to approximately 10 000 MI patients/year) that report to the SWEDEHEART registry. The centres will be randomized 1:1:1 to three clusters: 1) reporting cardiac rehabilitation structure and process variables to SWEDEHEART every six months (audit intervention) and being offered implementation support to implement guidelines on secondary prevention (implementation support intervention); 2) audit intervention only; or 3) no intervention offered. Baseline cardiac rehabilitation structure and process variables will be collected. The primary outcome is an adherence score measuring centre-level adherence to secondary prevention guidelines. Secondary outcomes include patient-level secondary prevention risk factor goal attainment at one-year after MI and major adverse coronary outcomes for up to five-years post-MI. Implementation outcomes include barriers and facilitators to guideline adherence evaluated using semi-structured focus-group interviews and relevant questionnaires, as well as costs and cost-effectiveness assessed by a comparative health economic evaluation.

**Discussion:**

Optimizing cardiac rehabilitation centres’ delivery of services to meet standards set in guidelines may lead to improvement in cardiovascular risk factors, including lifestyle factors, and ultimately a decrease in morbidity and mortality after MI.

**Trial registration:**

ClinicalTrials.gov. Identifier: NCT05889416. Registered 2023-03-23.

**Supplementary Information:**

The online version contains supplementary material available at 10.1186/s13012-024-01366-8.

Contributions to the literature
Structured implementation support to improve guideline adherence has not previously been assessed within cardiac rehabilitation.The study is a national open-label cluster-randomized effectiveness-implementation hybrid trial including all cardiac rehabilitation centres that report to a national quality registry.The aim is to evaluate whether regularly reporting cardiac rehabilitation structure and process variables through a national quality registry and/or offering cardiac rehabilitation centres structured support to implement guidelines on secondary prevention will lead to an increase in centre-level adherence to guidelines on secondary prevention and improve patient-level outcomes.

## Background

Cardiovascular risk factor reduction and the fostering of a healthy lifestyle after an acute myocardial infarction (MI) are the most effective interventions to prevent recurrent coronary events [1]. Administering these interventions via structured and comprehensive cardiac rehabilitation (CR) programmes reduces mortality, morbidity, unplanned hospital admissions, and improves health-related quality of life [2–4]. CR is a complex intervention, combining the optimal use of cardio-protective medication, exercise training, patient education, and behavioural modification to improve lifestyle, and psychosocial counselling [5, 6]. Patient participation in CR after an MI is given the highest recommendation and level of evidence in current guidelines on cardiovascular disease (CVD) prevention [1]. However, referral rates to CR programmes are generally low and patients´ treatment target attainment is sub-optimal [7]. While treatment target attainment rates at Swedish CR centres is on average among the highest in Europe, there are considerable differences in CR service delivery between centres [8–11] and consequently, large variations in patient-level outcomes between centres [12].

The SWEDEHEART registry is a nationwide quality registry that records baseline characteristics, treatments, and outcomes of patients with MI admitted to coronary care units in Sweden [13]. Follow-up data describing secondary preventive patient-level outcomes have been collected in the CR part of the registry (SWEDEHEART-CR) since 2005 [14]. However, only a handful of variables monitoring centre-level structure and processes are included in the registry.

In 2019, a National Working Group on Secondary Prevention was commissioned by the Swedish Association of Local Authorities and Regions to author National Guidelines on Secondary Prevention for patients with coronary artery disease, aiming to decrease the variation in secondary prevention delivery and outcomes in Sweden. The guidelines were published in February 2022 [15]. In parallel with the release of CR guidelines, the SWEDEHEART-CR Working Group proposed incorporating variables into the registry to assess the recommended structure and processes outlined in the guidelines [16].

The Swedish healthcare system is highly decentralized, where overall healthcare policies and guidelines are set by national regulating agencies, and the responsibility for providing and funding services, lies with 21 autonomous regions [17]. Each regional authority is responsible for implementing the 2022 National Guidelines on Secondary Prevention on a local level. Implementing guidelines is, however, a complex process faced with many challenges, and often revised guidelines result in little or no change in clinical practice [18, 19]. To address the disparity between policies and clinical practice, the aims of the study are following:

*Primary aim*

To prospectively study whether a) audit and feedback of CR structure and processes within the SWEDEHEART registry and b) supporting CR centres in implementing CR guidelines can increase centre-level guideline adherence.

*Secondary aims*

To cross-sectionally evaluate the association between centre-level adherence to guidelines and patient-level outcomes.To prospectively study whether audit and feedback of CR structure and processes within the SWEDEHEART-CR registry can improve patient-level outcomes.To prospectively evaluate whether supporting CR centres in implementing CR guidelines can improve patient-level outcomes.To qualitatively evaluate barriers and facilitators to guideline implementation.To evaluate cost and cost-effectiveness of the implementation support.

## Method

### Study setting and recruitment

The study started in October 2023 and will include all CR centres (*n* = 78) which report to the SWEDEHEART-CR registry. The sole exclusion criterion for CR centres is unwillingness to participate. The inclusion criteria for patients are 1) having a diagnosis of a type 1 MI (caused by atherosclerotic plaque rupture or coronary artery thrombosis) and 2) age 18–79 years at discharge from MI hospitalization. There are no exclusion criteria for patients.

### Study design

The study is an open-label cluster-randomized effectiveness-implementation hybrid trial. The effectiveness-implementation hybrid design allows for testing an implementation strategy while observing the intervention´s impact on patient outcomes [20]. For the implementation support, the Consolidated Framework for Implementation Research (CFIR) model will be used to guide the design [21, 22]. Normalization Process Theory (NPT) will be used to guide the exploration of the implementation process [20].

### Randomization

Centres will be randomized 1:1:1 to three clusters (A, B and C). Randomization will be stratified by geographical healthcare district (two districts in each stratum). Randomization will be performed by an independent organisation not involved in the study to avoid site-selection bias.

### The interventions

First, baseline structure and process variables will be administered through the SWEDEHEART-CR registry at all CR centres. Second, two clusters will receive one of two interventions (A and B) and one cluster will receive no intervention (control cluster) (C) (Fig. 1):

A)Reprting CR structure and process variables through the registry every six months and being offered structured implementation support (audit intervention + implementation support intervention).B)Reporting CR structure and process variables through the registry every six months but no structured implementation support being offered (audit intervention).C)No reporting of CR structure and process variables, and no structured implementation support offered (control).

**Fig. 1 Fig1:**
[figure not shown]
Overview, process and timeline of the study

### The audit intervention

The audit intervention (clusters A and B) involves, on centre-level, reporting 30 variables on CR structure and processes, measuring adherence to the National Guidelines, to the SWEDEHEART registry. The complete list of CR structure and process variables is available in Additional file 1.

### The implementation support intervention

For the implementation support intervention (cluster A) facilitators from the research team will provide hands-on support and guidance to the CR team as they work to implement changes [23]. Facilitators are physicians and nurses experienced in the field of cardiac rehabilitation. In the recruitment step, the centre directors or key stakeholders will be contacted by the principal investigator to offer study participation by means of an e-mail. Upon acceptance to participate, the time to start the intervention will be determined, a timeline established, and the CR centre director will be asked to allocate time in the schedule for the relevant CR staff to work on the study. The implementation support will be conducted in four steps: 1) evaluation of centre practice, 2) identification of areas in need of improvement, 3) implementation of change, and 4) follow-up (Table 1). The implementation objects are work routines or CR programme components listed in Additional file 1 identified as sub-optimally implemented at the respective CR centre. Implementation strategies (defined by results from the Expert Recommendations for Implementing Change (ERIC) project) used will be identifying and preparing champions, identify barriers and facilitators, facilitation, distribution of educational materials, conducting educational meetings, organizing clinician implementation team meetings, and, providing local and technical assistance [23–28].

**Table 1 Tab1:** The steps of the implementation support intervention

Steps of implementation support	Description of activities at each participating centre
Evaluation of centre practice	- The CR team (physicians, nurses, and physiotherapists) responds to a questionnaire listing aspects contributing to a best-practice CR model as defined in the National Guideline for Secondary Prevention [15] (Additional file 1). Using the responses current practice is evaluated the centre´s adherence to each object quantified on an ordinal scale (yes, partly, no). - Each member of the CR team responds to the Normalisation Measure Development (NoMAD) questionnaire [29].
Identification of areas in need of improvement	- Answers to the questionnaire listing aspects contributing to a best-practice CR are assessed by the facilitators from the research team and summarized in a report, also including feedback on possible areas of improvement. - The CR team receives a copy of the report. - Semi-structured focus group interviews performed on-site to identify barriers and facilitators to guideline implementation.
Implementation of change and run-in period	- An implementation is plan drafted. - Implementation assistance planned, prepared, and provided by the research team, with active participation of the healthcare personnel at the CR centre.
Study period	- Implemented changes followed for 4 months. Regular contact provided by the facilitators, assisting the centres in solving problems that can arise when adapting to new working routines.
Follow-up	- Each member of the CR team responds to the NoMAD questionnaire [29]. - Semi-structured focus group interview performed by the facilitators, to evaluate the implementation process.

The implementation support will be provided during a two-day visit from the facilitators, two follow-up phone calls during the first month after the visit, up to three educational meetings (number as requested by centre personnel), and a digital follow-up meeting 4 months after the initial visit. Additional phone or video calls, and emails will be provided as needed.

### Primary effectiveness outcome

The primary endpoint is an “adherence score”, measuring adherence to the National Guidelines on Secondary Prevention [15]. The adherence score is partly derived from the 30 variables capturing guideline-directed CR structure and processes incorporated into the SWEDEHEART-CR registry in October 2023. Permissible values are yes/partly/no/unknown. Additionally, the adherence score will include nine process variables that measure a) patient attendance in various CR components (number of patients attending a CR programme component divided by the number of patients eligible for participation), and b) time between MI hospitalization discharge and start of different CR programme components, already audited in SWEDEHEART:

*Attendance in CR components*
Proportion of patients attending an initial CR assessment (nurse visit).Proportion of patients attending an individual visit to a physiotherapist after discharge before starting an exercise-based CR (EBCR) programme (a pre-exercise screening visit).Proportion of patients completing a 3-month EBCR programme.Proportion of patients attending an individual close-out visit to a physiotherapist after completing an EBCR programme (a post-exercise assessment visit).Proportion of patients attending a patient education programme.Proportion of patients attending a close-out CR visit with a nurse at one-year after MI.*Time (days) to start of different components of CR*7.Time from hospital discharge to initial CR assessment (nurse visit).8.Time from hospital discharge to the pre-exercise screening visit to a physiotherapist.9.Time from pre-exercise screening visit to start of EBCR programme.

The responses will be pooled at each site into an adherence score for each CR centre. The contribution of each variable to the score will be weighed depending on the importance of each measurement, based on level of recommendation in European guidelines [1].

### Secondary effectiveness outcomes

Table 2 displays secondary outcomes, encompassing both short- and long-term patient outcomes and implementation outcomes. Implementation outcomes will be based on responses gathered through the customized Normalisation Measure Development (NoMAD) questionnaire [29] and insights obtained from focus group interviews, as well as a cost-effectiveness analysis.

**Table 2 Tab2:** Secondary outcomes

Outcomes	Cluster	Measures	Data source	Timing
Short-term patient-level outcomes	All clusters	- Blood pressure (mmHg). - LDL-C (mmol/L). - Self-reported statue of health measured using EuroQol-VAS (0–10). - Self-reported smoking status (never/ prior [> 1 month smoke-free]/active) - Self-reported dietary habits (four questions with Likert scale 0–3 points, total score 0–12 points). - Self-reported physical activity (the number of days during the last week the patient has been physically active for a minimum of 30 min [at least 10 min at a time] with activity causing shortness of breath and a slightly increased pulse, corresponding to a brisk walk). - Completing an exercise-based CR programme for at least 3 months (yes/no)	The SWEDEHEART registry	Baseline and one-year after the start of intervention
		- Adherence to secondary prevention medication	Pharmaceutical registry	Baseline and one-year after the start of intervention
Long-term patient-level outcomes	All clusters	Total mortality Major adverse cardiovascular events (MACE) consisting of the following: - cardiovascular mortality - non-fatal MI - non-fatal ischemic stroke - coronary revascularization - hospitalization for new or worsening heart failure	National Patient Registry and the Cause of Death Registry	Up to 5 years after the end of the intervention
Centre-level implementation outcomes	Cluster A	- Barriers - Facilitators	Semi-structured focus group interviews	At the start and the end of implementation support period
		- Implementation cost and cost effectiveness.	A comparative health economic evaluation	At the start and the end of implementation support period

*LDL-C* low-density lipoprotein cholesterol, *VAS* visual analogue scale, *CR* cardiac rehabilitation, *MI* myocardial infarction

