### Data analysis

In the primary outcome analysis of the audit intervention, CR centres in clusters B and C will be compared. All CR centres that have responded to the CR structure and process variables will be included in the analysis. For the primary outcome analysis of the implementation support intervention CR centres in clusters A and B will be compared. All CR centres that have i) provided answers to the structure and process variables and that ii) have scores in the lower two tertiles of the adherence score at baseline will be compared. Our analyses will assume intention-to-treat principles by treating intervention assignment as randomized regardless of whether the intervention had uptake within the practice. If not all centres in cluster A accept implementation assistance, a per-protocol analysis will be performed including only those centres in study group A that accept implementation assistance.

For the secondary analyses on patient outcomes, all patients that attended at least two follow-up visits within CR will be included. For the outcome analysis of the audit intervention patients followed at CR centres in clusters B and C will be compared. For the outcome analysis of the implementation support intervention patients followed at CR centres in clusters A and B will be compared. A per-protocol analysis will be performed including only patients belonging to CR centres in cluster A that accept implementation assistance.

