### Quantitative data

For baseline characteristics descriptive statistics will be used (means +/-standard deviation, medians [quartile 1, quartile 3], proportions [%] and ranges). For the primary outcome analysis, given randomized treatment assignment, total adherence scores at end of follow-up as well as change in scores between baseline and follow-up will be compared using linear regression analysis. In the case of unequal randomization concerning CR centre size (small < 75 patients/year, medium 75–150 patients/year or large > 150 patients per year), geography (6 geographical districts in Sweden, two in each stratum) or the centres belonging to a university hospital (yes/no), adjusted multivariable analysis will be performed. Results will be reported as relative treatment effects (odds ratios) with 95% confidence intervals. For secondary outcome analysis on short-term patient outcomes, the same statistical methods will be used, applying linear (continuous) or logistic (binary) regression analyses. For long-term outcomes (major adverse cardiovascular events [MACE] and total mortality) Cox proportional hazards regression models will be performed, reporting hazard ratios with 95% confidence intervals. In case of missing data, imputation will be considered. For all quantitative analyses a two-sided test of statistical significance will be used with an alpha level of 0.05.

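### Smoking is compared in all patients without using baseline smoking, which dilutes any cessation effect; a binary endpoint among smokers at the index MI would be sharper

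*Protocol article*

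**What the plan says.** All references are to the protocol article.

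- **Outcome.** Table 2, under Secondary effectiveness outcomes, lists smoking among the short-term patient-level measures as "Self-reported smoking status (never/ prior [> 1 month smoke-free]/active", timed at "Baseline and one-year after the start of intervention".
- **Model.** The Quantitative data section carries the primary-outcome methods over to the short-term patient outcomes, "applying linear (continuous) or logistic (binary) regression analyses". It gives no dichotomy for smoking and no ordinal or multinomial model.
- **Population.** The Data analysis section says that for patient outcomes "all patients that attended at least two follow-up visits within CR will be included". Study setting and recruitment adds that "There are no exclusion criteria for patients", so smoking status plays no part in eligibility either.
- **Comparisons.** Clusters B and C are compared for the audit intervention, and A and B for implementation support.
- **Covariates.** Adjustment is conditional ("In the case of unequal randomization concerning CR centre size", geography or university-hospital status). All three are centre characteristics; a patient's baseline smoking is not listed.

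The Abstract speaks of attaining risk factor goals at one year, but the Methods never turn this into a goal for smoking.

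**The concern.** For smoking, the main thing rehabilitation can change is whether a patient who smoked at the time of the MI has stopped a year later. Never-smokers and long-standing ex-smokers have almost no room to improve. If the three levels are collapsed to active versus not active and compared in everyone, these patients stay in the denominator. They shrink the difference, while the difference that remains must be detected against the variation of the whole population.

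The share of patients who smoked at the MI also varies between centres. With about 26 centres per cluster, that share will differ somewhat between arms by chance. An unadjusted all-patient comparison carries this difference into the one-year result. At stake is the precision and readability of one secondary outcome.

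**Working it through.** **Inputs.** The article gives no smoking prevalence, quit rate, between-centre spread or target effect for smoking, so there is no stated figure to reproduce. The following are assumptions: share smoking at the MI, s = 20% to 40%; quit rate by one year 50% in one arm and 55% or 60% in the other; between-centre SD of s of 3 to 8 percentage points. From the article: 78 centres randomised 1:1:1, so 26 per cluster; about 10,000 patients a year, so roughly 10,000/3 = 3,333 per cluster per year.

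**Dilution.** If only smokers at the MI can be active at one year, the active share among all patients is s × (1 − quit rate), and the arm difference is s × (difference in quit rates). Let q be the quit rate averaged over the two arms and p = s(1 − q) the average active share in all patients. For the same N patients per arm:

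- z in all patients ∝ s(q₁ − q₀) / √[2p(1 − p)]
- z in smokers ∝ (q₁ − q₀) / √[2q(1 − q)/s]

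The squared ratio, smokers over all patients, simplifies to (1 − p)/q.

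| s | Quit rates | Active, all patients | Difference, all | Difference, smokers | p | q | (1 − p)/q | z ratio |
|---|---|---|---|---|---|---|---|---|
| 20% | 50% vs 55% | 10% vs 9% | 1 point | 5 points | 0.095 | 0.525 | 1.72 | 1.31 |
| 20% | 50% vs 60% | 10% vs 8% | 2 points | 10 points | 0.09 | 0.55 | 1.65 | 1.29 |
| 40% | 50% vs 55% | 20% vs 18% | 2 points | 5 points | 0.19 | 0.525 | 1.54 | 1.24 |
| 40% | 50% vs 60% | 20% vs 16% | 4 points | 10 points | 0.18 | 0.55 | 1.49 | 1.22 |

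So the all-patient comparison has an expected z lower by a factor of 1.22 to 1.31, equivalent to needing 1.5 to 1.7 times as many patients.

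**Cross-check by required sample size** (two-sided 5%, 80% power, clustering ignored). With s = 25% and quit rates of 50% and 60%, the comparison among smokers needs 388 smokers per arm, who come from 388/0.25 = 1,552 patients. The all-patient comparison of 12.5% with 10.0% needs 2,507 per arm. The ratio is 2,507/1,552 = 1.62, inside the range above.

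**Chance imbalance.** With 26 equally weighted centres per arm and half of smokers persisting, the chance SD of the arm difference in active smoking at one year is 0.5 × SD × √(2/26):

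- SD 3 points: 0.42 points
- SD 5 points: 0.69 points
- SD 8 points: 1.11 points

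For illustration, suppose there is no true effect and 25% versus 28% smoked at the MI. The active shares at one year are 12.5% and 14.0%, an odds ratio of 1.14. The chance SD of the difference at the MI is 0.8 to 2.2 points, so a 3-point gap is plausible only towards the upper end of the assumed spread.

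**The case against.** **The coding is a measure, not an endpoint.** Table 2 describes how the variable is recorded, goal attainment is naturally binary, and an analysis plan that is not shown may name a dichotomy. This stands as far as the model is concerned. A reader might infer that smoking cannot be analysed by the stated methods at all. The article does not support that, because active versus not active fits logistic regression. The mismatch alone would be a small gap. The population is different: the article states one for all patient outcomes and makes no exception for smoking.

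**Change from baseline may already be covered.** The Quantitative data section analyses change in adherence scores and says the same methods apply to short-term patient outcomes. But no change is defined for a categorical status, so this wording does not supply a cessation endpoint.

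**Randomisation balances smoking.** A reader might infer a built-in bias from differences in who smoked at the MI. The article does not support that either. Centres are randomised, so what remains is chance imbalance between few clusters, which is noise. With mid-range assumptions (30% smokers, a 7.5-point gain, SD 5 points) it is 0.69 points against a diluted effect of 0.30 × 7.5 = 2.25 points.

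**All-patient active smoking is a legitimate outcome.** It also captures relapse: someone recorded as an ex-smoker may be only just over one month smoke-free and can return to smoking. An analysis restricted to smokers at the MI would miss this. The point stands and is a reason to keep the all-patient analysis in a supporting role.

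**Power may be ample anyway.** At s = 25% and a 10-point gain, 2,507 per arm compares with roughly 3,333 patients per cluster per year. That is before the two-visit rule and clustering by centre, and a 5-point gain at the same s would need 10,513 per arm. The margin is not secure.

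**The baseline is tied to the intervention.** The timing in Table 2 refers to the start of the intervention and does not establish that baseline means status at the index MI. This stands and must be confirmed.

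**Conclusion.** The point holds as a loss of sharpness in one secondary outcome. As the article stands, smoking would be compared in all patients with at least two visits, without using baseline status, and a cessation effect would be diluted. Under the assumed rates the difference falls from 5-10 points to 1-4 points and the expected z is lower by a factor of 1.22 to 1.31. Chance differences between centres in smoking at the MI add an SD of about 0.4 to 1.1 points if prevalence varies between centres by 3 to 8 points. That is comparable only to the smallest diluted effects.

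All these sizes rest on assumed prevalence, quit rates and between-centre spread. The z ratios also ignore clustering, which would raise the required numbers in both populations. The direction of the dilution follows from the arithmetic whenever few non-smokers can change status. The primary outcome is not affected.

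**What to change.** 1. In Table 2, state the smoking endpoint as smoke-free for more than one month at one year, yes or no, among patients recorded as active smokers at the index MI. Analyse it by the logistic regression already planned.
2. Confirm that the registry baseline is each patient's smoking status at the index MI, and say so in the timing column.
3. Keep active smoking at one year in all patients, adjusted for baseline smoking status, as a supporting analysis. It captures relapse and removes most of the case-mix noise.
4. Report the three-level status descriptively.

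The cost is a change of wording, provided that step 2 is confirmed. The restricted analysis contains fewer patients; under the assumed rates the undiluted effect more than makes up for this. Settling the endpoint before patient data are analysed also avoids a later choice about how to collapse the categories.

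### Completion of exercise-based rehabilitation is both an item of the adherence score and a patient-level outcome, so for that one outcome the planned cross-sectional association is partly built in

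*Protocol article*

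**What the plan says.** Three places in the protocol article matter.

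- **Primary effectiveness outcome.** The score combines 30 registry variables with nine more: "the adherence score will include nine process variables that measure a) patient attendance in various CR components" and "time between MI hospitalization discharge and start of different CR programme components, already audited in SWEDEHEART". Item 3 of the nine is "Proportion of patients completing a 3-month EBCR programme". Attendance items are defined as "number of patients attending a CR programme component divided by the number of patients eligible for participation". On weights: "The contribution of each variable to the score will be weighed depending on the importance of each measurement". No numerical weights are given.
- **Secondary effectiveness outcomes, Table 2.** Under short-term patient-level outcomes, with SWEDEHEART as the source, the table lists "Completing an exercise-based CR programme for at least 3 months (yes/no".
- **Background, secondary aims.** The first secondary aim is "To cross-sectionally evaluate the association between centre-level adherence to guidelines and patient-level outcomes".

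For the secondary analyses of patient outcomes, the Data analysis section states that "all patients that attended at least two follow-up visits within CR will be included". No section removes completion from the score, or from the outcomes, for the cross-sectional aim.

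**The concern.** If an outcome is one of the parts summed into the exposure, the two correlate even when the other parts are unrelated to the outcome. For completion of exercise-based cardiac rehabilitation (EBCR), the reference value of no association is then not zero. Item 4, the close-out physiotherapist visit, is close to the same problem, because by its definition it takes place after the programme has been completed.

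At stake is how one result is read. A positive association between the score and EBCR completion could be reported as evidence that guideline-adherent centres achieve better patient outcomes, when part of it is the item correlating with itself.

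**Working it through.** The article states no figure for this analysis, so there is none to reproduce. The check has two parts.

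**1. Where the overlap lies.** Completion of a three-month EBCR programme appears in the score as a centre proportion and in Table 2 as a patient-level yes/no variable, both from SWEDEHEART. The other patient outcomes in Table 2 (blood pressure, LDL cholesterol, EuroQol-VAS, smoking, diet, physical activity, medication adherence, mortality, cardiovascular events) are not among the nine process variables. The overlap is not exact: item 3 is taken over eligible patients, and the patient analyses over those with at least two follow-up visits.

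**2. How large the built-in part could be.**

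Inputs from the article: score SD 2.4 and maximum 39 (Sample size calculations, from eight centres); 78 centres (Study setting and recruitment); two-sided alpha 0.05 (Quantitative data).

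Assumptions: the weight w of item 3, from 1 to 3; its between-centre SD, from 0.05 to 0.25 as a proportion; total score SD held at 2.4; item 3 independent of the rest of the score; the association treated as a correlation across centres.

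Write the score as S = wX + R, with X the item and R the rest, independent of X. Then Cov(X, S) = w·SD_X², so

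r = w·SD_X / SD_S = w·SD_X / 2.4.

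| SD of item 3 | w = 1 | w = 2 | w = 3 |
|---|---|---|---|
| 0.05 | 0.02 | 0.04 | 0.06 |
| 0.10 | 0.04 | 0.08 | 0.13 |
| 0.25 | 0.10 | 0.21 | 0.31 |

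An alternative that does not set w and SD_X separately: 39 independent items of equal variance give r = 1/√39 = 0.16. With a total SD of 2.4 this needs an item SD of 2.4/√39 = 0.38, which is very wide for a centre proportion at weight 1.

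The chance of p < 0.05 when nothing but the built-in part is present, by Fisher's z with n = 78, is Φ(z − 1.96) + Φ(−z − 1.96), where z = atanh(r)·√75:

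- r = 0.02: about 5%
- r = 0.10: about 14%
- r = 0.16: about 29%
- r = 0.31: z = 0.323 × 8.66 = 2.80, so Φ(0.84), about 80%

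With item 3 removed from the score, the built-in r under the same independence assumption is 0.

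**The case against.** The strongest counter-argument is that the cross-sectional analysis is barely specified. The aim is one line. It does not name the patient outcomes that enter, and the Data analysis section sets out only the randomised contrasts. The abstract summarises the patient outcomes as risk factor goal attainment and major coronary events, without EBCR completion. An analysis plan that is not shown may use a reduced score. This limits the weight of the point but does not remove it. The aim speaks of patient-level outcomes, Table 2 places EBCR completion under that label, and following the text as written produces the overlap.

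The objection on size stands. At weight 1, anchored to the stated SD, the effect may be negligible.

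Three stronger readings are tempting, and the documents do not support them.

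- **A significant result is close to certain.** If the pre-exercise visit, completion and post-exercise visit moved together perfectly, in a score of 39 equal-variance items that are otherwise independent, r would be 3/√(36 + 9) = 0.45 and the chance of p < 0.05 about 99%. Nothing in the article says these items are perfectly correlated. In the same equal-variance model, correlations of 0.3 to 0.7 between completion and the two visits, and between the visits, give r = (1 + 2ρ)/√(39 + 6ρ) = 0.25 to 0.37. That model still rests on the wide item SD noted above.
- **The whole exercise pathway is tautological.** Items 2, 8 and 9 (the pre-exercise visit and the two times to start) are centre processes. Whether they go with completion is an empirical question that the aim may properly ask, and removing them from the main analysis could discard real exposure.
- **The trial's effect estimates are biased.** The randomised contrasts compare arms on each outcome separately and stay valid. The shared item means only that the score and EBCR completion are not independent pieces of evidence.

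**Conclusion.** The point holds in a narrow form: one short-term outcome in one secondary, observational aim. For a score that keeps item 3, the built-in contribution is positive, but its size is unknown. It is about 0.02 to 0.10 in correlation at weight 1 and up to about 0.31 at weight 3, with 0.16 under equal-variance independent items, against a null value of 0. These figures rest on assumed weights and an assumed between-centre SD, on a score SD from eight centres that is held fixed as the weight changes, and on item 3 being independent of the rest of the score. The differing denominators make the overlap substantial rather than complete. This is a minor point, worth settling before the analysis because it is easily avoided.

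**What to change.** For the cross-sectional aim, state that when EBCR completion is the outcome, the adherence score is computed without item 3 (programme completion) and without item 4 (the post-exercise visit). Alternatively, leave EBCR completion out of that analysis. The full score can stay for the other named outcomes.

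A version that also drops items 2, 8 and 9 can be a sensitivity analysis. Using only the 30 structure and process variables as the exposure would be another option, but their content is in Additional file 1, which was not available here, so it should first be checked for EBCR completion items.

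The cost is one reduced score from data already collected. The primary outcome, the randomised analyses and the sample size do not change.
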